## Abstract

**Introduction:**

Reductions in exacerbation and hospitalisations are the outcomes rated as most important by people with chronic obstructive pulmonary disease (COPD). Most COPD management is currently based on a reactive approach, and delays in recognising treatable opportunities underpin COPD care quality gaps. Innovations that empower COPD self-management, facilitate integrated clinical care and support delivery of evidence-based treatment interventions are urgently required.

**Methods and analysis:**

The Remote-Management of COPD: Evaluating the Implementation of Digital Innovation to Enable Routine Care trial is a prospective observational cohort hybrid implementation and effectiveness study that will explore the adoption of a digital service model for people with ‘high-risk’ COPD and evaluate the feasibility of this approach versus current standards of care. People with COPD, who have had recent severe exacerbation and/or COPD–obstructive sleep apnoea overlap or chronic hypercapnic respiratory failure requiring home non-invasive ventilation (NIV) or continuous positive airway pressure (CPAP), with internet access will be recruited into the study and enrolled into the digital service.

Study endpoints will examine participant utilisation, clinical service impact and clinical outcomes compared with historical and contemporary control patient data. The digital infrastructure will also provide a foundation to explore the feasibility of approaches to predict outcomes and exacerbation in people with COPD through machine learning analysis.

**Ethics and dissemination:**

Ethical approval for this clinical trial has been obtained from the West of Scotland Research Ethics Service. The trial will commence in September 2019 for a duration of 2 years. Results will be presented at local, national and international meetings, as well as submission for publication to peer-reviewed journals.

**Trial registration number:**

NCT04240353.

## Introduction

Chronic obstructive pulmonary disease (COPD) is a common, preventable and treatable disease, which is characterised by persistent respiratory symptoms and airflow limitation. The main risk factor for COPD is tobacco smoke but other environmental exposure may contribute. Respiratory symptoms include breathlessness, cough and/or sputum production. These symptoms are under-reported by patients.^1 2^ COPD may be punctuated by periods of acute worsening of these respiratory symptoms, often referred to as exacerbation, that can result in emergency department (ED) attendance or hospital admission. For many patients, COPD is associated with significant comorbidity, which increases its morbidity and mortality.

COPD is a major healthcare challenge, with worldwide rising prevalence. The Global Burden of Disease Study reported a prevalence of 251 million cases of COPD globally in 2016.^3^ It was projected to be the fourth leading cause of death worldwide by 2020.^4^ Reductions in exacerbation and hospitalisations are the outcomes rated as most important by patients with COPD.^5^ Effective delivery of evidence-based interventions for COPD—smoking cessation, influenza vaccination, pulmonary rehabilitation, personalised inhaled therapy, home oxygen therapy (where indicated) and home non-invasive ventilation (NIV, where indicated)—has been shown to reduce exacerbation and hospital admission.^6^ There are considerable barriers to uptake and delivery of these interventions.^7^ This care quality gap particularly affects outcomes from COPD exacerbation. Exacerbation is the main driver of healthcare costs (estimated annual National Health Service (NHS) cost of managing COPD is £1.9 billion.^8^ There is an urgent requirement for an innovation-based service redesign that can integrate care to deliver these evidence-based interventions and achieve reductions in COPD exacerbation and admissions.

Self-management also plays a key role in the treatment of COPD.^9^ Patients who can be successfully taught and supported with COPD self-management show a significant reduction in COPD admissions.^10 11^ The process of establishing a multidisciplinary community respiratory team in NHS Greater Glasgow & Clyde (NHS GG&C), which supports self-management in patients identified acutely as being high risk of hospital admission, has been associated with reduction in hospital admission rates.^12^

While interventions should be developed for patients with all severities of COPD, it is logical to target immediate efforts towards patients with ‘high-risk’ COPD, that is, those who are at most risk of exacerbation and hospital admissions. Established data indicate that patients with COPD who have had severe exacerbation (one requiring ED attendance or hospital admission) in the previous 12 months and/or have persisting hypercapnic respiratory failure requiring home NIV fall into this high-risk group.^6 13^ Interventions proven in this group can then be rolled out (if cost-effective) to the lower risk groups of patients with COPD.

### Digital service model

Pilot data from NHS GG&C have highlighted the potential for digital innovations to predict COPD outcomes and support treatment uptake. Using qualitative methods, Slevin *et al* highlighted patient acceptance to take an active role in self-management using digital health technology with the potential for healthcare professionals to provide meaningful preventative care.^14^ Web and smartphone-based apps have shown the capability to facilitate disease self-management and support uptake of interventions.^15 16^ Although patient-focused digital tools currently exist for COPD, there is a limited evidence base for their use, with evaluations mainly performed in isolation and not integrated with established clinical services or statutory electronic health records (EHRs).

Most COPD management is currently based on a reactive approach, and delays in recognising treatable opportunities underpin COPD care quality gaps. For example, patients with COPD exacerbation typically have symptom deterioration for 2 days before seeking assistance, and then a potential delay of 2–5 days in accessing clinical care.^1^ Several studies have indicated the ability of regularly recorded patient-reported outcomes (PROs) and home NIV parameters to predict outcomes, including exacerbation and treatment success/failure in patients with COPD.^17 18^ Changes in activity measured by wearable devices have been shown to predict outcomes after COPD exacerbation.^19^ Currently, symptom diaries and other PRO questionnaires, activity, exercise and NIV data are obtained in routine practice in NHS GG&C. However, patient and clinician engagement is not consistent, data are not acquired systematically and are not often visible or actionable at key time points of patient–clinician interaction. These shortfalls, and the arising care quality gaps, could potentially be addressed by digitising this routine clinical care, improving the patient–clinician interface for data entry, and collating the acquired data.

Patient–clinician communication for COPD management, including supporting self-management, is currently dependent on face-to-face scheduled consultations, answer phone/email asynchronous messages from patient to clinician, and unstructured advocacy triggered or initiated communication from clinician to patient. These present several inefficiencies and risks. They could be overcome by digitalising the patient–clinician messaging system to support scheduling, remote management and support COPD self-management.

Home NIV successfully improves admission-free survival in patients who have persisting hypercapnic respiratory failure following life-threatening COPD exacerbation, with a number needed to treat of seven patients.^20^ NHS GG&C has successfully matched the outcomes from the HOT-HMV randomised clinical trial in our service adoption pilot delivering home NIV to eligible patients with COPD, using routinely available digital technologies (adaptive ‘auto-NIV’ modes, two-way remote monitoring via ResMed AirView platform).^21 22^ The challenge is to extend the evidence for this approach and obtain a service adoption playbook to enable this to be adapted and delivered at scale, by other clinical teams, within COPD integrated care.

Machine learning analysis and modelling based on available data shows significant promise in COPD predictive management. Data available in patient’s EHR at triage assessment can robustly predict outcome (admission, length of stay) from severe COPD exacerbation.^23 24^ The addition of physiology measurements to EHR data improves machine learning predictive model performance in other clinical conditions.^25^ Further evaluation of these analytics and predictive modelling, in a comprehensive dataset including PROs, physiology data and clinical events, is a logical step to determine their potential role in real-time or near real-time clinical use.

### Objectives

Innovations which can empower patient self-management, facilitate integrated clinical care and support delivery of evidence-based treatment interventions are urgently required. In the Remote-Management of COPD: Evaluating the Implementation of Digital Innovation to Enable Routine Care (RECEIVER) trial, we propose to explore the implementation of a platform which digitalises these as additional—potentially assistive—components alongside routine clinical care. In our endpoints, we will determine participant utilisation, clinical service impact and clinical outcomes, to evaluate the feasibility of this approach versus current standards of care. A digital infrastructure for this support of routine clinical care would also provide a foundation to explore the feasibility of approaches to predict outcomes and exacerbation in patients with COPD, to be tested in future prospective clinical and regulatory trials.

Our aims are to establish a digitalised service model for ‘high-risk’ patients with COPD which will:

Integrate current routine clinical care within a digitally enabled remote management service infrastructure.Enable delivery of remote management of COPD at scale within the NHS and other healthcare systems.Capture relevant routinely acquired PROs, continuous physiology data and clinical event/episode data in a patient and clinician co-designed interface which enables engagement.Facilitate evolution from a reactive to a proactive and preventative COPD service model.

### Digital service components

The digital service model will sit alongside routine clinical care, aiming to assist and enhance current patient management. Key components of proposed digital service model for COPD are noted and summarised in figure 1. Tabulated information in online supplemental material 2 outlines how the RECEIVER trial components would be used in addition to current routine clinical care.

10.1136/bmjresp-2021-000905.supp2Supplementary data

**Figure 1 F1:**
[figure not shown]
RECEIVER Digital Service ComponentsCOPD, chronic obstructive pulmonary disease; EHR, electronic health record; NHS GG&C, National Health Service Greater Glasgow & Clyde; NIV, non-invasive ventilation; PROs, patient-reported outcomes; SMS, Short Message Service.

The COPD digital service components being used in the RECEIVER trial are:

Patient-facing web portal: this has been co-designed with patients and captures PROs and provides access to standard COPD self-management content. It also includes a messaging facility which can be patient or clinician initiated. Examples of visuals available on supporting website (https://support.nhscopd.scot).Patient wearable device: Fitbit Charge 3 device (CE marked).Remotely monitored home NIV: provision of this is our current standard of care for patients with hypercapnic respiratory failure, using AirView NIV remote management platform (ResMed). We have integrated our COPD digital service platform with the AirView platform, so that it acquires the NIV data unmodified for review where available. NIV therapy management will continue to be conducted through the AirView platform: the RECEIVER trial COPD platform is not used to modify or enhance patient NIV therapy.User-designed clinical dashboard: presents integrated data with an aim of facilitating improvement in provision of guideline-based COPD care, and supporting COPD self-management.Patient–clinician asynchronous messaging: to support routine clinical care.NHS GG&C Azure cloud-based digital architecture: this provides and integrates the above services with existing NHS GG&C electronic healthcare systems. Diagram of digital architecture included in online supplemental material 3.

10.1136/bmjresp-2021-000905.supp3Supplementary data

## Study methods and analysis

### Study design

This study is a prospective observational cohort hybrid implementation and effectiveness study.^26^ It will be performed according to the UK Policy Framework for Health and Social Care Research (2020).^27^ The clinical intervention component is regarded as a phase IV adoption study. Data visualisation to facilitate guideline-based care, supported self-management and home NIV are evidence-based COPD interventions.

In this study, we will evaluate the adoption of digitally integrated remote management service innovations to support routine clinical care. Implementation of these will be evaluated and the digital innovations will be iterated to optimise them, based on user experience accrued during the study. We will acquire a consented dataset for trial endpoint analysis including exploratory machine learning-based predictive modelling. The machine learning analysis will also allow us to prioritise data inputs for follow-up study.

Secondary outcomes for the RECEIVER cohort will be compared with those from matched cohorts of patients acquired from the NHS GG&C SafeHaven dataset. Ethics approval is in place to access this large database of de-identified data, to establish a control cohort from a historical time series and a RECEIVER trial concurrent time series. These cohorts will be matched for demographics, COPD severity and hospital admission frequency with the RECEIVER cohort.

We will conduct a substudy of additional baseline and follow-up physiological measurements (oscillometry, parasternal electromyography (EMG), home pollution monitoring) in patients in whom it is feasible to obtain these during their hospital admission and/or hospital attendance alongside their routine clinical care.

Additionally, we will conduct a substudy of clinical users, with platform tracking analytics to measure clinician time spent on the platform, and user experience data. Clinical team members involved in the delivery of patient support using the digital service will be eligible for inclusion and appropriate consent will be sought. The qualitative components will be acquired through semistructured group or 1:1 interviews conducted by trained members of the research team. Thematic analysis will be performed. Anonymised transcripts will be coded, and themes generated from the codes. Themes will be discussed within the research team to reach agreement and add rigour.

An overview of the study design is provided in figure 2.

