### Study population

People with high-risk COPD attending secondary care in the North and South Sectors of NHS GG&C will be screened for inclusion in this study.

Inclusion criteria:

Confirmed diagnosis of COPD, established prescreening or at screening, defined as per Global Initiative for Chronic Obstructive Lung Disease (GOLD) 2020 guidelines.^6^Home NIV cohort: hypercapnic respiratory failure and/or sleep disordered breathing, meeting established criteria for provision of home NIV.Exacerbation cohort: presentation within last 12 months with severe or life-threatening exacerbation of COPD, defined as per GOLD 2020 guidelines.^6^Participant or close contact who has daily access to smartphone, tablet or home computer with internet access.Informed consent.>18 years of age.

Exclusion criteria:

Inability to comprehend informed consent.Communication barrier precluding use of COPD digital service.

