## Study outcome measures

Primary and secondary endpoints for the RECEIVER Study are shown in table 1.

**Table 1 T1:** RECEIVER primary and secondary endpoints

Primary endpoint	Proportion of enrolled high-risk participants with COPD who use remote management in a digital service model
Secondary endpoints	Clinical outcomes, comparing impact of digitally enabled remote management versus historical and contemporary SafeHaven cohorts: Clinical events: COPD exacerbation; unscheduled care contact (digital platform, COPD team visit, primary care, emergency department, hospital admission); mortality—COPD and non-COPD related. Hospital occupied bed days preceding and subsequent 12 months (adjusted time interval if survival <12 months). Treatment uptake (where indicated): smoking cessation; pulmonary rehabilitation; vaccination; supported self-management; home oxygen; home NIV. NIV group: NIV usage, symptom change, NIV therapy parameters, blood gases during routine clinical care. Supported self-management: utilisation of self-management information (page views), number of exacerbation managed at home versus in hospital, number of rescue packs used in 12 months (captured through weekly PROs), utilisation of messaging (number of message threads), sputum microbiology (where available during routine clinical care), impact of patient activation measures (where measured during routine care). Impact of demographics, physiology and patient activation measures (where measured during routine care)—deprivation category of area of residence, age and sex, number of previous admissions, smoking status, participation in pulmonary rehabilitation in previous 2 years; lung function measurements, modelled home air pollution exposure; EMG, oscillometry and home air pollution monitoring in subset of participants where this is carried out—on outcomes, clinical events and treatment uptake. Clinical service outcomes for digital service model, remote-managed home NIV and supported self-management: Remote-managed home NIV: number, nature and complexity of NIV therapy reviews and interventions to provide. Supported self-management: number, nature and complexity of reviews and interventions to provide. Digitalised service model: user and developer time/cost required for development and modification of clinical dashboard; qualitative analysis (clinical user satisfaction and reflection on efficiency or additional workload); quantitative analysis (clinical dashboard utilisation tracking). Patient portal: user and developer time/cost required for development and modification of clinical dashboard; qualitative analysis (user satisfaction) and quantitative analysis (uptake, engagement with app and wearable, successful use of digital service vs bypass to conventional healthcare contacts). Machine learning-supported exploratory analyses of associations and relative predictive importance of electronic health record, PROs, wearable physiology and NIV parameters: Associations between changes in PROs (MRC, CAT, symptom diary, and EQ-5D-5L questionnaires) with routine clinical care interventions, COPD exacerbation and other clinical events. Associations between changes in wearable monitoring parameters (activity, sleep, heart rate variability, energy expenditure, respiratory rate) with routine clinical care interventions, COPD exacerbation and other clinical events. Associations between changes in NIV-monitored parameters (usage, leak, airway pressures, respiratory rate, tidal volume, minute ventilation, inspiratory/expiratory ratio and detected respiratory events) with routine clinical care treatment interventions, COPD exacerbation and other clinical events. Associations between changes in clinical endpoints and relative importance plots of all remote management-acquired data (including EMG, oscillometry and home pollution monitoring exploratory endpoints in subgroup these measured on) to determine contribution of these to outcome prediction, and therefore value of these for future prospective study. Patient-centred outcomes: Health-related quality of life (EQ-5D-5L) at baseline and monthly during study. Qualitative user research (planned subset of participants, convenience sample) with semistructured user experience interviews. Impact of patient activation (where this is measured at baseline and/or follow-up during routine clinical care) on enrolment and use of digital service model. Healthcare cost analyses: Development and installation costs for digitalised service model for remote management of COPD. Recurring costs (clinical staffing, digital platform hosting, digital platform scheduled update and maintenance) for digital service model for remote management of COPD. Projected direct and indirect cost-savings (admission and unscheduled care reduction, travel, carer burden impact, clinical efficiency) of high-risk COPD with digitally enabled remote management, compared with previous service model.

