## Statistics and data analysis

Secondary outcomes in the RECEIVER observational cohort will be compared with matched retrospective data from de-identified linked datasets of historical control and contemporary control high-risk patients with COPD. These will comprise of patients identified from coding and admission data as having had severe exacerbation of COPD between 1 January 2010 and 30 April 2019 (historical cohort) and between 1 July 2019 and 30 June 2020, excluding participants enrolled in the RECEIVER Study (contemporary control). The historical control dataset will contribute to machine learning models development. Secondary outcome analysis will be separately compared between the RECEIVER cohort, historical cohort and contemporary control cohort. This component of the study is also separately registered with dataset access approval from NHS GG&C SafeHaven LPAC.

The clinical endpoint data will be reported as a proportion and 95% CI for that outcome, calculated by Kaplan-Meier method. Demographic data will be presented as mean and SDs, or medians and IQRs as appropriate. Correlation, t-test, analysis of variance and effect size analyses will be used as appropriate for secondary endpoint analysis, comparing results of clinical endpoint and patient-centred outcomes with NIV therapy and supported self-management parameters.

Machine learning ensemble methods will be used to develop binary classification problems for patient risk. Precision, recall, accuracy and C-statistics of the receiver operating characteristic curve will be used to evaluate model performance.

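### RECEIVER recruits through a home NIV route that neither control cohort has, so background NIV and hypercapnic severity can be mixed into the admission, bed-day and mortality comparisons

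*Protocol article*

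**What the plan says.** **Entry to RECEIVER.** The abstract (Methods and analysis) gives the routes as "recent severe exacerbation and/or COPD–obstructive sleep apnoea overlap or chronic hypercapnic respiratory failure requiring home non-invasive ventilation (NIV", with CPAP as the alternative device. Study population lists two cohorts. One is the exacerbation cohort, with a severe or life-threatening exacerbation in the past 12 months. The other reads "Home NIV cohort: hypercapnic respiratory failure and/or sleep disordered breathing, meeting established criteria for provision of home NIV".

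**Control selection.** Statistics and data analysis takes historical controls from patients "identified from coding and admission data as having had severe exacerbation of COPD between 1 January 2010 and 30 April 2019". The same rule gives the contemporary controls, "between 1 July 2019 and 30 June 2020, excluding participants enrolled in the RECEIVER Study (contemporary control". Neither has an NIV route.

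**Matching.** Study design states: "These cohorts will be matched for demographics, COPD severity and hospital admission frequency with the RECEIVER cohort".

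**Home NIV.** The Introduction (Digital service model) credits it with better admission-free survival when hypercapnic failure persists after a life-threatening exacerbation, "with a number needed to treat of seven patients". Digital service components lists remotely monitored home NIV as a component. The same entry calls it current standard care and adds that "the RECEIVER trial COPD platform is not used to modify or enhance patient NIV therapy".

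**The comparison.** Table 1 describes the secondary clinical outcomes as "comparing impact of digitally enabled remote management versus historical and contemporary SafeHaven cohorts". They include admissions, mortality and occupied bed days. Home NIV uptake is listed there as an outcome too.

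**The concern.** The two sides of the comparison are assembled by different rules. A person can enter RECEIVER on the NIV criterion without a recent severe exacerbation, whereas every control must have had one. None of the three stated matching categories names NIV use, hypercapnia or NIV indication.

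The protocol itself treats home NIV as affecting admission-free survival, which is also where Sample size projects the benefit of the service. Two distortions are possible. If severity is matched well, NIV users in RECEIVER may be set against similar patients without NIV, and part of the NIV effect would appear as a service effect. If severity matching misses hypercapnia, NIV-route participants may be sicker than their matches, and the service would look worse than it is. At stake is whether the admission, bed-day and mortality contrasts can be read as the impact of the digital service.

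**Working it through.** There is no figure in the plan to reproduce. The only number is recruitment of 400, and Sample size expressly declines a power calculation.

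**Step 1: the rules side by side.**

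| | RECEIVER | Historical control | Contemporary control |
|---|---|---|---|
| Severe exacerbation route | yes | yes | yes |
| Home NIV/CPAP route | yes | no | no |
| NIV use or indication named for matching | – | no | no |

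Participants who qualify only by the second row have no control selected on the same basis.

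**Step 2: the treatment part.** Inputs:
- Number needed to treat of 7 (Introduction), so the absolute difference is 1/7 = 14.3 points of admission-free survival. The article gives no time horizon for it; I assume it applies over the follow-up.
- NIV shares are not given for either cohort. Assumed: 10% to 40% in RECEIVER, 5% in controls.

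Formula: shift = (share in RECEIVER − share in controls) × 14.3.
- 10% vs 5%: 0.05 × 14.3 = 0.7 points
- 20% vs 5%: 0.15 × 14.3 = 2.1 points
- 30% vs 5%: 0.25 × 14.3 = 3.6 points
- 40% vs 5%: 0.35 × 14.3 = 5.0 points

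Equal shares give 0.

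**Step 3: the severity part.** Suppose NIV-indicated patients would, untreated, have admission-free survival *s* points worse than their matches (*s* assumed). Then net shift = share difference × (14.3 − *s*). At 30% vs 5%:
- *s* = 10: 0.25 × 4.3 = +1.1 points
- *s* = 14.3: 0
- *s* = 20: 0.25 × (−5.7) = −1.4 points
- *s* = 30: 0.25 × (−15.7) = −3.9 points

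The sign changes within a plausible range.

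**Step 4: against sampling error.** Control numbers are not given. Take 400 or 1,600, event probability 0.5 and independent groups.
- 400 vs 400: 1.96 × √[0.25 × (1/400 + 1/400)] = 6.9 points
- 400 vs 1,600: 1.96 × √[0.25 × (1/400 + 1/1,600)] = 5.5 points

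A 3.6-point shift lies inside both half-widths but is not negligible. With no service effect, a two-sided 5% test would reject about 17% of the time (400 vs 400) or 25% (400 vs 1,600). More controls narrow the interval around the shifted value.

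**The case against.** The strongest reply is that NIV belongs to what is being evaluated. Digital service components lists remotely monitored NIV, Study design names home NIV among the evidence-based interventions, and Table 1 makes its uptake an outcome. This stands in part. NIV started because of the service should not be adjusted away, and a reader who infers that NIV lies wholly outside the service goes further than the text. NIV already in place at enrolment, however, cannot be an effect of enrolment.

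Second, a reader might infer that NIV is certainly commoner in RECEIVER and that its benefit will be credited to the service. The documents support neither as fact. No shares are reported, and contemporary controls come from the same health board, where home NIV is already standard care. The number needed to treat covers only persisting hypercapnia after a life-threatening exacerbation, while the NIV route also admits sleep-disordered breathing. Step 3 shows that the bias can run either way.

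Third, COPD severity is undefined in the article and might capture respiratory failure, and the control component has a separate registration that is not shown. This is fair, and details of matching can be left to such a document. The different selection rules, though, are stated in the article and are not a matter of missing detail.

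Fourth, only secondary outcomes are affected, and Study limitations acknowledges inherent bias and disclaims definitive proof. That limits the weight of the point, but the caveat is general and does not mention this imbalance, which can be reduced cheaply.

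**Conclusion.** The point holds as a mismatch of selection rules. NIV-route participants lack like-for-like controls, and the stated matching set does not name the variable on which the groups differ by design. Differences in background NIV and hypercapnic severity can therefore enter the admission, bed-day and mortality contrasts.

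The treatment part alone is about 0.7 to 5.0 points of admission-free survival. That rests on assumed NIV shares and on an upper-end use of the number needed to treat. The net effect, including severity, may be smaller, zero or negative, so it would be wrong to conclude that the comparison is biased in favour of the service. The primary endpoint, utilisation, has no control comparison and is unaffected. The change is worth making before the comparison is run, but does not threaten the feasibility aim.

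**What to change.** For the admission, bed-day and mortality outcomes:

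1. Make the main control comparison the RECEIVER participants who meet the exacerbation-cohort criterion, since they satisfy the same kind of selection rule as the controls. Report those who entered only by the home NIV route separately, descriptively or against controls of the same kind. The trial already holds the entry-route data.
2. Where control data allow, also match or stratify on home NIV/CPAP use or indication (such as documented hypercapnic failure) at time zero. Use alone is not enough: Study population admits people who meet NIV criteria, and those who start after enrolment would be counted as non-users. Table 1's uptake comparison already requires NIV data in controls, although the extract listed under EHR data does not name them.
3. Leave NIV started after time zero uncontrolled, because uptake is a declared outcome.
4. State whether background NIV counts as part of the service, reconciling its listing as a component with the statement that the platform does not modify it.

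The cost is a smaller main comparison, a sparse NIV stratum, and possibly incomplete NIV records for historical controls going back to 2010. The article does not show that the remote-monitoring records can be linked to de-identified controls, so item 2 is conditional. Item 1 does not depend on it.
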